### Care as usual

Patients in the control group receive care as usual. No recent guidelines for the systematic assessment of psychosocial problems in cancer patients exist at the Institute Verbeeten. In the control group, radiotherapists may refer patients to psychosocial caregivers (social workers) at the Institute Verbeeten. However, this occurs according to the radiotherapist's judgment about the presence or absence of psychosocial problems in patients. Referrals to psychosocial caregivers at the Institute Verbeeten will be registered in both the patient's records and by the psychosocial caregivers.

### Recruitment of the study population

Recruitment of cancer patients takes place at the Institute Verbeeten, a radiation oncology department in Tilburg, the Netherlands. Only cancer patients receiving RT are eligible for this study.

The following inclusion criteria are used: 1) patients with the most common cancer types such as lung, prostate, bladder, rectum, breast, cervix, endometrial, skin carcinoma and Non-Hodgkin; 2) patients 18 years of age or older and 3) patients with no metastases. Exclusion criteria are: 1) patients receiving palliative treatment, ≤ 10 fractions of RT; 2) patients unable to read and speak Dutch and 3) patients unable to complete questionnaires. Patients who meet the inclusion criteria are sent information about the study. Those willing to participate in the study are asked to sign a consent form and are only allowed to participate after completing and returning it.

### Randomisation and stratification

To reduce contamination bias, radiotherapists, instead of patients, are randomly allocated to the experimental or control groups. First, the radiotherapists are stratified according to the general percentages of incoming patients they referred to a (psychosocial) caregiver in the period 2006–2007. Within their stratum, they are either randomly assigned to the experimental or to the control condition (see Figure 2). Thus, in both conditions there are equal numbers of radiotherapists who previously referred relatively more and less cancer patients to (psychosocial) caregivers. Patients are linked to their radiotherapist. Therefore, they are randomised to the experimental condition with or without pre-measurement or to the control condition with or without pre-measurement through their radiotherapist (see Figure 2). Patients who visit their radiotherapists in odd weeks are assigned to the experimental/control condition with a pre-measurement and patients who visit their radiotherapists in even weeks are assigned to the experimental/control condition without a pre-measurement. Radiotherapists of the experimental condition are asked not to discuss this study with their colleagues of the control condition.

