**Methods/Design:**

A CRCT is developed using a Solomon four-group design (two intervention and two control groups) to evaluate the effects of using the SIPP. Radiotherapists, instead of cancer patients, are randomly allocated to the experimental or control groups. Within these groups, all included cancer patients are randomised into two subgroups: with and without pre-measurement. Self-reported assessments are conducted at four times: a pre-test at baseline before the first consultation and a post-test directly following the first consultation, and three and 12 months after baseline measurement. The primary outcome measures are the number and types of referrals of cancer patients with psychosocial problems to relevant (psychosocial) caregivers. The secondary outcome measures are patients' satisfaction with the radiotherapist-patient communication, psychosocial distress and quality of life. Furthermore, a process evaluation will be carried out. Data of the effect-evaluation will be analysed according to the intention-to-treat principle and data regarding the types of referrals to health care providers and patient satisfaction about the with radiotherapists will be analysed by means of descriptive techniques. The process evaluation data will also be analysed by means of descriptive techniques.

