### Statistical analysis

Descriptive techniques will be used to describe patients' background characteristics. To detect potential differences between the experimental and control groups at the start of the study, the baseline levels of psychological distress and quality of life will be compared. Furthermore, to identify potential differences between the two experimental groups and the two control groups (both with and without pre-measurement) at T3 the extent of psychological distress and quality of life will be compared. If these latter differences emerge, the four groups need to be handled separately in the analyses, i.e. the experimental and control groups with pre-measurement and the experimental and control groups without pre-measurement will be compared separately. If not, the two experimental groups and the two control groups will be combined in one group.

Data of the effect evaluation will be analysed according to the intention-to-treat principle. Univariate, multivariate and descriptive techniques are applied to estimate the effect of the intervention by comparing the experimental with the control groups with regard to the primary and secondary outcomes at the follow-up measurements and by comparing the pre-test (T1) with post-tests (T3 and T4). Potential confounding factors and baseline differences will be checked and included in the model if necessary. Since dependency between outcome variables from the same cluster may exist, as well as between repeated measurements within patients, multilevel modelling will be carried out. Furthermore, multilevel modelling minimizes the loss of data through dropout by including all available data from participants in the analyses. Dropout will be described.

The process evaluation data (collected from radiotherapists and patients of the experimental groups) will be analysed by means of descriptive techniques.

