## Discussion

This study will provide insight into the actual systematic effects of using the SIPP in consultation settings. It is important to know the possible effects of using the SIPP on aspects such as communication between physicians and patients, early recognition and treatment of psychosocial problems, the extent and severity of experienced psychological problems among cancer patients and the quality of life of patients over a long period. Until now, there have been no RCTs on the effectiveness of the SIPP on aspects such as quality of life among cancer patients and the extent of psychological distress that cancer patients experience over a long period after the initial radiation or other treatment of the cancer. Until now, there have also been no reports on the differences in number of patients receiving psychosocial help because of using the SIPP.

The design of this study is a CRCT. Cluster randomisation is applied because randomisation at the patient level may jeopardise the validity of the study since patients of the experimental and control conditions may visit the same radiotherapist for consultation. Furthermore, radiotherapists may alter their communication style, attitude or may pay more attention to patients' psychosocial distress because of using the SIPP. The Solomon four-group design is chosen in order to check for potential pre-measurement effects on intervention outcomes [52,53].

In this study, we decided to include patients with the most common cancer types and with a reasonably good prognosis because patients were asked to complete questionnaires 12 months after baseline measurement.

One limitation of this study is that the results can not be generalised to all Dutch cancer patients since our study population consisted of cancer patients that received RT. Further studies outside the radiotherapy setting would be required to generalise the results.

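### Allocation to pre-measurement is called randomised but follows odd and even calendar weeks, which weakens the with/without pre-measurement contrast (not SIPP versus control)

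*Protocol article*

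**What the plan says.** The Methods/Design part of the abstract states that "all included cancer patients are randomised into two subgroups: with and without pre-measurement". The section Randomisation and stratification uses the same word for patients: "they are randomised to the experimental condition with or without pre-measurement or to the control condition with or without pre-measurement through their radiotherapist". It then gives the working rule: "Patients who visit their radiotherapists in odd weeks are assigned to the experimental/control condition with a pre-measurement". Those seen in an even week get none. The only step described as random is that of the radiotherapists: "Within their stratum, they are either randomly assigned to the experimental or to the control condition".

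The pre-measurement factor has two uses. The Discussion gives the reason for it: "The Solomon four-group design is chosen in order to check for potential pre-measurement effects on intervention outcomes". The Statistical analysis section compares the groups with and without pre-measurement on distress and quality of life at T3 and attaches a decision to the result: "If these latter differences emerge, the four groups need to be handled separately in the analyses". If no difference is seen, the two experimental groups are combined and so are the two control groups.

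**The concern.** Week parity is systematic allocation. Once the appointment date is set, the subgroup is fixed and can be known to anyone who books, invites or sees the patient. Under Recruitment of the study population, patients are sent information and "are only allowed to participate after completing and returning it", meaning the consent form. The article does not say whether the form comes back before the visit week is fixed, so enrolment that differs by week type is not ruled out. Anything that follows a fortnightly pattern would also be confounded with pre-measurement.

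At stake is the meaning of the with/without contrast. If odd-week and even-week patients differ, a T3 difference may reflect who was enrolled and not the effect of being measured beforehand. The four groups would then be kept apart for the wrong reason, and the report would claim randomisation for a factor that was not randomised.

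**Working it through.** **1. Label against rule.**

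| Factor | Called | Mechanism described |
|---|---|---|
| SIPP v control | randomised | radiotherapists assigned at random within strata of past referral rate |
| Pre-measurement v none | randomised | odd week: yes; even week: no |

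Given the visit week, the probability of pre-measurement is 1 or 0. The label in the second row is therefore wrong.

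**2. The plan's own sample size** (Sample size and power analysis). Inputs: 2% v 11%, one-sided 0.05, power 80%. With pooled variance and mean proportion 0.065:

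- n = [1.645 × √(2 × 0.065 × 0.935) + 0.842 × √(0.02 × 0.98 + 0.11 × 0.89)]² / 0.09² = 91.7, so 92 per condition.
- 4 × 92 = 368; 368 × 1.13 = 415.84; 415.84 / 0.80 = 519.8, so 520.

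The stated figures reproduce. Random allocation in the same 1:1 split would leave 520 unchanged.

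**3. Numbers in the contrast.** 520 × 0.80 = 416 patients after dropout; 416 / 4 = 104 per group. Within each arm the contrast is 104 with v 104 without pre-measurement, assuming an equal split.

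**4. What a spurious difference would do.** The article gives no figure for a week-type difference and no significance level for the pooling check. Assume a standardised difference δ and a single two-sided 5% test, ignoring clustering. The noncentrality is δ × √(104/2) = δ × 7.21, and the chance of triggering is about Φ(δ × 7.21 − 1.96) + Φ(−δ × 7.21 − 1.96).

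| Assumed δ (SD) | δ × 7.21 | Chance of triggering |
|---|---|---|
| 0 | 0 | 0.05 |
| 0.1 | 0.72 | 0.11 |
| 0.2 | 1.44 | 0.30 |
| 0.3 | 2.16 | 0.58 |

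The plan compares several scales in two arms, so the chance that at least one comparison triggers is higher in every row.

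**5. Cost of a false trigger.** The analysis moves from 208 v 208 (2 × 104) to two comparisons of 104 v 104. The standard error of each is larger by √2 = 1.41. On the plan's referral rates, before clustering, power is Φ[(0.09 × √n − 0.573) / 0.343]. This is 0.97 at n = 184 (two groups of 92 combined) and 0.80 at n = 92.

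**6. Can imbalance be checked?** Table 1 restricts T1 to the groups with pre-measurement. HADS (14 items), GHQ-12 (12) and QLQ-C30 (30), 56 items in all, therefore have no baseline in half the patients. Age, gender, marital status and education (T2), and cancer site, chemotherapy, TNM and KPI (records), carry no such restriction.

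**The case against.** The strongest reply is that the trial's question is SIPP versus control. That comparison rests on randomised radiotherapists, and the week rule is identical in both arms. Even if the groups are wrongly kept apart, each comparison is still experimental against control within the same week type. A false trigger therefore mainly costs precision, and the sample size was built as four times 92, so the 80% planned power per comparison already allows for separate analysis. All of this stands.

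The selection routes are also conjecture. The article mentions no fortnightly rota, no rebooking between weeks and no invitation that reveals the subgroup. The burden argument is modest: everyone completes the 56 items at T3 and T4, so pre-measured patients complete 168 items and the others 112. The Statistical analysis section provides for checking confounders and baseline differences, and the background variables allow part of that check. This also stands, but it does not reach baseline distress or quality of life in unmeasured patients, or unrecorded selection.

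A further point in the plan's favour is that a week-type shift of equal size in both arms cancels, on an additive scale, from the interaction of pre-measurement with condition. It does not cancel from the within-arm comparisons that the plan uses for its pooling decision.

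A reader might infer that the trial is not truly randomised, or that the SIPP effect is biased. The documents do not support either reading.

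**Conclusion.** The point holds in limited form. The allocation to pre-measurement is described as randomised and is not; this follows from the article's own text and needs no assumption. It applies to all 520 patients. The consequence is confined to the with/without pre-measurement contrast and the pooling decision that hangs on it. SIPP versus control is not directly affected.

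The size of any bias cannot be derived, and nothing shows that selection took place. The 30% trigger rate is an illustration that rests on an assumed 0.2 SD difference, an assumed two-sided 5% criterion and 104 per group; over 0.1 to 0.3 SD it runs from 11% to 58%, against 5% with no difference. The weakness of letting a preliminary test decide pooling would exist under full randomisation too and is not counted here. The change should be made, but the trial's main conclusion does not depend on it.

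**What to change.** - **Wording.** In the abstract and under Randomisation and stratification, replace *randomised* by *allocated by calendar week (quasi-random)* for the pre-measurement factor. Keep *randomised* for the radiotherapists.
- **Reporting.** By week type and arm, give the numbers invited and consenting, and the socio-demographic and medical variables collected in all groups.
- **Analysis.** Treat the with/without contrast as a non-randomised comparison and do not let it alone decide pooling. Keep pre-measurement as a factor in the planned multilevel model, and report its interaction with condition as an estimate with a confidence interval.
- **Patients still to be enrolled** (recruitment runs to July 2009). Use a concealed random order of weeks, or a concealed list within radiotherapist opened after consent.

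The first three cost wording, two tables and one model specification; N stays at 520. The last adds some logistics and creates two allocation regimes within this factor, to be handled by an indicator for enrolment period. If that is judged not worth doing late in recruitment, the first three still apply.

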**Figure 2 F2:**
[figure not shown]
**Cluster randomised control trial – Solomon four-group design**.

### Sample size and power analysis

This study is powered on the primary outcome measures, i.e. the effect of the SIPP on the number and types of referrals of patients with psychosocial problems to relevant (psychosocial) caregivers. Sample size calculation shows that 92 patients per condition are required to compare the number of referred patients to (psychosocial) caregivers between conditions with a 80% power and a significance level of 0.05 (one-sided) [28]. This calculation is based on results reported by Pruyn and colleagues [23]. In their study, the use of the Integral Checklist resulted in more referrals from 2 to 11%. This means that for our study a total of 368 patients have to be included for the analyses.

The consequence of adopting a CRCT is that the outcome for each patient can no longer be assumed as independent [26]. Such a lack of independency has implications for study size and power [29]. The standard sample size has to be inflated to take account of the cluster design by using an estimate of the Intra Cluster Correlation [30,25,26,31]. For our study, no appropriate ICC was available. Therefore, as in the CRCT of Cumming and colleagues [32], we assume an ICC of 0.005 as appropriate because the variance of our outcome measurements between clusters can be considered low compared to the variability between the patients within a cluster. To retain power, the standard sample size should be multiplied by the design effect (d, d = 1+ρ (m-1)), where m is the size of a cluster unit and ρ the ICC [25,33]. We therefore multiplied our standard sample size with a design effect (d) of 1.13. With an expected dropout rate of 20%, the corrected sample size for the CRCT is determined at 520.

It is to be noted that stratification by baseline value of the outcome variable decreases the sample size required [31]. In our study, radiotherapists are stratified according to the general percentages of incoming patients they referred to a (psychosocial) caregiver. Stratification of this primary outcome variable reduces the between-cluster variability in the primary outcome. In a study by Elridge and colleagues the sample size required decreases of almost 50% by using stratification of the primary outcome [31]. To be on the safe side regarding the power of our study we decided not to correct for stratification of the radiotherapists. Recruitment and data collection is anticipated to continue for 24 months.

### Measures

#### Outcome measures

Table 1 presents the primary and secondary outcome measurements and time of assessment.

**Table 1 T1:** Primary and secondary outcome measures of the effect evaluation

Variables	No. of items	T1	T2	T3	T4
**Primary outcome measures:**					
Number and types of referrals	8/NA	-	-	Q	Q/DR
**Secondary outcome measures:**					
Patients' satisfaction with the radiotherapist-patient communication	5	-	Q	-	-
Extent of psychological symptoms:					
Symptoms of anxiety and depression (HADS)	14	Q	-	Q	Q
General psychological distress (GHQ-12)	12	Q	-	Q	Q
Quality of life (EORTC QLQ-C30)	30	Q	-	Q	Q
**Additional variables:**					
Socio-demographic variables	4	-	Q	-	-
Medical variables	4	-	-	-	DR

T1: Before first consultation (baseline, only groups with pre-measurement); T2: After consultation;

T3: Three months after baseline; T4: 12 months after baseline; N/A: not applicable; Q: questionnaire:

DR: data record.

HADS: Hospital Anxiety and Depression Scale [16]; GHQ-12: General Health Questionnaire-12 items [17];

EORTC QLQ-C30: European Organisation for Research and Treatment of Cancer,

Quality of life Questionnaire 30 items [46].

#### Primary outcome measures

The primary outcome measures are the number and types of referrals of patients with psychosocial problems to psychosocial workers at the Institute Verbeeten and/or to external health care providers (e.g. psychologists, psychiatrists). The number and types of referrals to (psychosocial) caregivers are measured at three months (T3) and 12 months (T4) after baseline assessment with a self-developed questionnaire by the patient and from registration records of the psychosocial caregivers at the Institute Verbeeten. This questionnaire comprises eight items on whether the patient is referred to a psychosocial caregiver and the types of problems the patient has experienced (e.g. financial, psychological, and sexual). The psychosocial caregivers at the Institute Verbeeten collect data from all referred patients, including types of problems, number of sessions needed and further referral to an external (psychosocial) caregiver.

#### Secondary outcome measures

The secondary outcomes are classified in three dimensions: 1) patients' satisfaction with the radiotherapist-patient communication during the first consultation; 2) extent of psychological symptoms at T3 and T4; and 3) patients' quality of life at T3 and T4.

*Patients' satisfaction with the radiotherapist-patient communication *is measured directly after the first consultation with the radiotherapist (T2) by the patient completing a self-developed questionnaire comprising five items. The first four items measure whether physical complaints, psychological complaints and social and sexual problems were discussed with the radiotherapist (item range 1 (yes) to 3 (no) plus "not applicable"). The fifth item measures the patient's general opinion (item range 1 (very bad) to 6 (very good)) about the communication with the radiotherapist during the first consultation.

*The extent of psychological symptoms *is measured with the Hospital Anxiety and Depression Scale (HADS) [16] and the Goldberg's General Health Questionnaire-12 item version (GHQ-12) [17]. Patients complete these self-reported questionnaires at baseline and at T3 and T4.

The HADS is a valid, reliable and useful instrument [16] that is widely used in studies among cancer patients [34-40]. It is considered unbiased by coexisting general medical conditions because its questions do not refer to somatic symptoms associated with depression [41]. The HADS consists of a brief subscale of anxiety and a subscale of depression. Both subscales comprise seven items. Ratings by patients are made on four-point scales (0–3, with 3 indicating greatest distress). Higher scores on each subscale indicate a greater presence of problems [16,42,43].

The GHQ-12 is a well-validated instrument [17] that has been used in numerous studies among cancer patients [34,36,44,45]. It is a standardised measure of psychiatric morbidity across a wide range of patients [43]. It was intended for use in general practice settings as a screening instrument for detecting verifiable psychiatric morbidity (generally anxiety and depression). It measures "usual state" rather than chronic (long-term) problems [43]. The GHQ assesses with 12 items whether the patient considers him- or herself better, the same, worse or much worse over the previous four weeks than he/she "usually" is. Those who indicate that their symptoms are unchanged or have decreased receive a score of 0, while those who report that their symptoms have increased receive a score of 1. Total scores range from 0 to 12 [17].

*Quality of life *is measured using the European Organisation for Research and Treatment of Cancer, Quality of life Questionnaire (EORTC QLQ-C30) [46]. The EORTC QLQ-C30 is validated and widely used [30,47-50]. It is a 30-item cancer-specific measure that assesses health-related quality of life. The EORTC QLQ-C30 comprises:

• five functional subscales: physical (five items), role (two items), emotional (four items), cognitive (two items) and social functioning (two items);

• a subscale about global health status and quality of life during the past week (two items);

• three symptom scales: nausea/vomiting (two items), fatigue (three items) and pain (two items); and

• six single items measuring appetite loss, insomnia, constipation, diarrhoea, dyspnoea and financial difficulties due to illness or treatment.

The items on the five functional scales and three symptom scales have four-point response choices of 1 (not at all), 2 (a little), 3 (quite a bit) and 4 (very much). Categories 3 and 4 are regarded as indicators of clinically-significant symptom levels. Both items of the subscale about global health status and quality of life use a seven-point visual analogue scale (VAS) ranging from 1 (very poor) to 7 (excellent) [43]. Patients completed the self-reported questionnaire EORTC QLQ-C30 at baseline and at T3 and T4.

